### Statistical methods

Three hundred and fifty participants will be required to detect at least a 20 % difference in the percentage of successes at 18 months post-randomisation (where success is defined as a device in use and ≥50 % CCIS improvement from baseline) between FENIX^TM^ MSA and SNS at 5 % level of significance, 90 % power, assuming approximately 40 % success on the SNS arm and allowing for 20 % loss to follow-up.

Analyses will be performed on an intention-to-treat (ITT) basis (primary analysis), where participants will be included according to the surgical procedure they were randomised to, and by actual treatment group, where participants will be included according to the surgery actually received (SNS device or FENIX^TM^ MSA device implantation). All hypothesis tests will be two-sided and use a 5 % significance level.

Analyses will exclude training cases, although data collected on training cases will be summarised. Analysis and reporting will be in line with Consolidated Standards of Reporting Trials (CONSORT) guidelines [26]. For the primary analysis, multi-level logistic regression will be used, including adjustment for the factors included in the minimisation algorithm.

Secondary endpoints including SF-12®, EQ-5D-5L®, CCIS and OD-score recorded at baseline and at 6, 12 and 18 months post-randomisation will be analysed using random effects (multi-level) models to account for the hierarchical nature of repeated measures data. The models will include adjustments for minimisation factors, and a categorical covariate will be used to assess the effect of length of time of device in use on these endpoints.

Pattern-mixture multi-level models, which will treat all participant data observed after the removal of their device (explant) as missing data, but also account for the informative nature of the missing data, will be fitted to the secondary endpoints outlined above. Note that this is in contrast to the random effects models outlined above, which incorporate data from participants ‘post-explant’. Therefore, the results yielded by the pattern-mixture multi-level models will act as sensitivity analyses, which can be used to explore the potential issue of disparity in treatment of participants post-explant in each treatment arm.

A subgroup analysis will be performed on participants in the FENIX^TM^ arm in order to explore which potential patients could benefit most from FENIX^TM^. A multi-level logistic regression model will be fitted using the primary endpoint, and the effects of various patient-level covariates (e.g. age, gender, baseline quality of life) on the odds of ‘success’ will be assessed.

Data collected on the safety of FENIX^TM^ MSA and SNS will be analysed using multi-level logistic regression. No formal interim analyses are planned; hence, no statistical testing will take place until final analysis.

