### Trial design

This is a UK multi-site, prospective, parallel group, randomised controlled, unblinded trial to evaluate the safety and efficacy of the FENIX^TM^ MSA for moderate to severe adult FI as compared to SNS. The Clinical Trials Research Unit (CTRU) at the University of Leeds will co-ordinate the trial. The follow-up period finishes 18 months after the last participant is randomised. The University of Leeds is the trial sponsor.

Participants will be randomised on a 1:1 basis to receive either FENIX^TM^ MSA or SNS. A computer-generated minimisation programme that incorporates a random element will be used to ensure treatment groups are well balanced for prognostic factors: treating surgeon, gender, severity of incontinence and degree of anal sphincter defect on endoanal ultrasound. (See Fig. 1: Trial schema).

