### Quality of life

Participants will complete a number of questionnaires designed to capture FI symptoms (CCIS) [15], constipation symptoms (OD score) [16], patient-reported quality of life data (Faecal Incontinence Quality of Life Questionnaire (FIQoL) [17], EQ-5D-5L® [18] and SF-12® [19]) and the costs involved with each treatment, including costs allocated for primary, community and social care services.

Participants will complete all questionnaires at baseline and at 6, 12 and 18 months post-randomisation. In addition, participants will complete the CCIS and the Health and Social Care Resource use Questionnaire 2 weeks post-operatively (only for temporary SNS, and FENIX^TM^ MSA). For the permanent SNS, participants will complete the Health and Social Care Resource use Questionnaire 2 weeks post-operatively.

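### The secondary repeated-measures models list baseline among the modelled visits and do not name the instrument's own baseline score as an adjuster, which can cost signal or precision

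*Protocol article*

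**What the plan says.** The protocol article, Statistical methods, states that secondary endpoints including SF-12, EQ-5D-5L, CCIS and OD score "recorded at baseline and at 6, 12 and 18 months post-randomisation will be analysed using random effects (multi-level) models", the reason given being the hierarchical structure of repeated measures. The covariates follow in the next sentence: "The models will include adjustments for minimisation factors, and a categorical covariate will be used to assess the effect of length of time of device". The categorical covariate is thus one for device-in-use time.

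The minimisation factors are listed under Trial design: "treating surgeon, gender, severity of incontinence and degree of anal sphincter defect on endoanal ultrasound". Baseline SF-12, EQ-5D-5L and OD score are not among them. How severity of incontinence is measured or grouped is not stated.

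Under Quality of life, the collection schedule reads: "Participants will complete all questionnaires at baseline and at 6, 12 and 18 months post-randomisation". A baseline value is therefore planned for every instrument.

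Pattern-mixture models are to be fitted to the same endpoints as sensitivity analyses, so they may inherit whatever handling of baseline is chosen. The article does not say whether baseline is a response or a covariate, whether there is a treatment-by-time term, or which contrast is the treatment effect.

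**The concern.** Baseline precedes treatment, so the expected difference between arms at that visit is zero. If it enters as a fourth outcome, the result depends on how the treatment term is written:

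- One treatment coefficient spanning all visits averages a known zero with the three informative differences.
- A separate effect per visit with a free baseline difference avoids that dilution. The 18-month contrast is then either a plain difference in levels, which ignores baseline, or a difference in change, which subtracts baseline in full. Each is less efficient than regression on baseline.

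Chance imbalance matters most for SF-12, EQ-5D-5L and OD score, which are not balanced by minimisation. A levels contrast leaves such imbalance uncorrected, and a change contrast over-corrects it. The device-in-use covariate arises after randomisation and cannot stand in for a baseline score.

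Quality of life is one of the trial's stated aims, and these models supply its between-arm estimates. At stake are attenuated estimates, or intervals wider than the data require.

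**Working it through.** **The plan's own figure.** The article gives no figure for the secondary models. Its sample size rests on a two-sided 5% test with 90% power, "assuming approximately 40 % success on the SNS arm and allowing for 20 % loss to follow-up", and a 20-point difference (40% against 60%). The normal-approximation formula with continuity correction gives 140 per arm, or 280 in total, and 280/(1 − 0.20) = 350. The stated 350 is reproduced, and nothing below alters it.

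**Inputs for the check.** From the article: one baseline and three follow-up visits (6, 12, 18 months), with 1:1 allocation. Assumed, because the article gives no values: equal variance at each visit, the same correlation r between any two visits, r from 0.3 to 0.7, complete data, a constant effect δ at all three follow-up visits, and no baseline information carried by the minimisation factors. Variances are in units of 2σ²/n, with n per arm.

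**1. One treatment coefficient over four visits.** With equal variances and correlations, generalised least squares weights the visits equally:

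(0 + δ + δ + δ)/4 = 0.75δ, whatever the value of r.

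The variance is (1 + 3r)/4. The baseline-adjusted mean of the three follow-up visits estimates δ with variance (1 + 2r)/3 − r². The ratio of expected z statistics is 0.75 × √{[(1 + 2r)/3 − r²] / [(1 + 3r)/4]}:

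- r = 0.3: 0.75 × √(0.443/0.475) = 0.72
- r = 0.5: 0.75 × √(0.417/0.625) = 0.61
- r = 0.7: 0.75 × √(0.310/0.775) = 0.47

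**2. Separate effect per visit, 18-month contrast.** The variance is 1 for a difference in levels, 2(1 − r) for a difference in change, and 1 − r² with baseline adjustment. The change-to-adjusted ratio simplifies to 2/(1 + r).

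| r | Levels / adjusted, 1/(1 − r²) | Change / adjusted, 2(1 − r)/(1 − r²) |
|---|---|---|
| 0.3 | 1/0.91 = 1.10 | 1.40/0.91 = 1.54 |
| 0.5 | 1/0.75 = 1.33 | 1.00/0.75 = 1.33 |
| 0.7 | 1/0.51 = 1.96 | 0.60/0.51 = 1.18 |

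In interval width, the change contrast is √1.54 = 1.24, √1.33 = 1.15 and √1.18 = 1.09 times the adjusted analysis.

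**3. Baseline as a response, arm means constrained equal at baseline.** Solving the generalised least squares equations gives an 18-month variance of 1.82, 1.50 and 1.02 in units of σ²/n. These equal 2(1 − r²) at the three correlations. There is no dilution, and the variance ratio to baseline adjustment is 1.00.

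**The case against.** The strongest reply is that the article does not specify the model being criticised. The sentence on visits closely tracks the collection schedule under Quality of life and may only describe when the data are recorded. The treatment term and the reported contrast are details that a condensed article commonly leaves to the full protocol or analysis plan, neither of which is shown. A constrained-baseline model fits the wording and loses nothing.

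Much of this stands, and it rules out three stronger readings that a reader might draw:

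- *That the models adjust for minimisation factors alone.* The same sentence adds the device-in-use covariate, and a list introduced by "The models will include adjustments for minimisation factors" need not be exhaustive. Severity of incontinence is itself a minimisation factor and probably carries part of baseline CCIS, though far less of the other three instruments.
- *That the treatment effect will be diluted.* The 75% figure needs a single coefficient over all four visits, and the article does not say that one will be used.
- *That the secondary estimates will be biased whatever the form.* Under a change contrast the estimate is unbiased and the cost is precision only.

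The reply does not remove the point. The article goes as far as naming the visits, the model class and covariates. It places baseline with the follow-up visits as data for a repeated-measures model and leaves the instrument's own baseline out of the named adjusters. A reader implementing that text could reasonably fit any of the three less efficient forms.

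**Conclusion.** The point holds conditionally. On its natural reading, the text makes baseline a repeated outcome without naming adjustment for it. The secondary models can then lose signal (about 25% of a constant effect with one common coefficient) or precision at 18 months (variance 18% to 54% higher for a change contrast, 10% to 96% higher for a levels contrast).

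The size rests on the assumed correlation of 0.3 to 0.7 and on equal variances and correlations across visits. It is smaller for CCIS to the extent that the severity factor captures its baseline, and nil if a common baseline mean is imposed. No consequence reaches the primary endpoint. This is a worthwhile clarification of the secondary analyses and does not threaten the trial's main conclusion.

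**What to change.** For SF-12, EQ-5D-5L, CCIS and OD score, state that the 6, 12 and 18 month values are the responses, with the same instrument's baseline value as a covariate, together with treatment, time, treatment-by-time and the minimisation factors. Name the 18-month between-arm contrast as the treatment effect. Equivalently, keep baseline as a response, constrain the arm means to be equal there, and report the same contrast. Say that the pattern-mixture models handle baseline in the same way.

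The cost is a few lines of wording. Baseline collection is already planned for every instrument, so no visit, data item or participant is added. The choice should be fixed before outcome data are seen, because the candidate forms would give different estimates or intervals.

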Recently, a new device for adult FI has been introduced into clinical practice—the FENIX^TM^ Magnetic Sphincter Augmentation Continence Restoration System (FENIX^TM^ MSA). It consists of a ring of 14 to 20 titanium beads with magnetic cores that are linked together to form an annular structure to be surgically placed around the anal sphincter complex. To defecate, the patient strains in a normal way and the force generated separates the beads to open the anal canal. Continence is restored by means of passive attraction of the beads. The FENIX^TM^ MSA costs £4000. Data on efficacy is limited to a few small single-centre studies [10, 11], a retrospective case-matched comparison to the artificial bowel sphincter where it compared favourably [12], and one small, multicentre, feasibility study [13] that suggests a ≥50 % improvement in continence in 70 % of patients in the short term. However, complications are reported in around 20 % of patients, leading to explantation in around 10 %.

In May 2012, the National Institute for Health Research Horizon Scanning Centre (NIHR HSC) reviewed the evidence on FENIX^TM^ MSA and concluded, “in order to determine its potential place in the pathway of care for FI larger long term studies of the safety, effectiveness and cost-effectiveness of FENIX^TM^ MSA in comparison to existing treatments are needed” [14].

In 2014, the NIHR HTA programme funded the SaFaRI trial—sacral nerve stimulation versus the FENIX™ magnetic sphincter augmentation for adult faecal incontinence: a randomised investigation (Trial Registration: ISRCTN 16077538). The aim of the trial is to undertake a randomised comparison of the FENIX^TM^ MSA as compared to SNS in terms of safety, efficacy, quality of life and cost-effectiveness. This manuscript details the trial design. The results are expected to provide rigorous data on FENIX^TM^ MSA, SNS and a “no treatment” group that fail temporary SNS and are treated by alternative means for the duration of trial recruitment. This will allow healthcare providers to make informed decisions about service provision and facilitate patient choice in the treatment options for FI.

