### Interventions

The control intervention of SNS implantation will be performed in accordance with each site’s usual practice. SNS implantation may be performed by either implantation of temporary stimulating electrode followed by TINED lead, or straight to TINED lead implant. A period of temporary stimulation is used to assess participant response, which is recorded by means of a 2-week bowel diary. Response is assessed in accordance with each site’s usual practice. The CCIS score will be recorded for trial purposes regardless of how response is assessed locally. If the response is positive (defined as a ≥50 % improvement in incontinence episodes or ≥50 % improvement in CCIS), the participant will proceed to a permanent implant. If the response is negative, the temporary device will be removed and the participant does not receive any further trial intervention but will continue follow-up for the required 18-month follow-up period.

FENIX^TM^ MSA implantation will be standardised in accordance with the manufacturer’s recommendations. Participants will receive a single dose of broad-spectrum intravenous antibiotics at induction of anaesthesia. Implantation of the device will be under fluoroscopic guidance. Participants will be provided with laxatives/stool softeners and analgesics for a period of 7–10 days post-operative.

Should a participant experience failure with either device, which requires explantation, they will not be permitted to undergo implantation of the alternative trial intervention during the 18-month post-randomisation follow-up period. The literature on SNS suggests that around 30 % of patients who undergo a trial of temporary SNS will not have a positive response and will not progress to a permanent implant. Within the trial setting, they will be treated according to current practice, allowing the range of treatments to be captured.

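### The secondary-endpoint models, as naturally read, adjust the arm comparison for time with the device in use, a post-randomisation variable, so the treatment effect they give is not the ITT effect

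*Protocol article*

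**What the plan says.** The Statistical methods section of the protocol article says that the repeated scores (SF-12, EQ-5D-5L, CCIS and OD score at baseline, 6, 12 and 18 months) "will be analysed using random effects (multi-level) models to account for the hierarchical nature of repeated measures data". The next sentence gives the terms in two clauses: "The models will include adjustments for minimisation factors", and then "a categorical covariate will be used to assess the effect of length of time of device in use on these endpoints". No second version of these models, without the device-time term, is mentioned.

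The same section makes intention to treat the primary basis of analysis. It also says that the random-effects models keep data collected after explantation, whereas the pattern-mixture sensitivity models set those data to missing.

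Three other statements determine how device time will be distributed:

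- SNS, Interventions: "around 30 % of patients who undergo a trial of temporary SNS will not have a positive response". For these participants "the temporary device will be removed and the participant does not receive any further trial intervention", but they stay in follow-up for 18 months.
- SNS, Background: a further 2–5% are explanted because of complications.
- FENIX, Background: "complications are reported in around 20 % of patients, leading to explantation in around 10"%. The article describes no test stage for this arm.

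**The concern.** Time with a device in use is a consequence of the allocated strategy, not a baseline characteristic. Whether a patient ends up with a working device is part of what the trial compares, and the primary endpoint itself requires a device in use. Holding device time fixed asks how the arms would differ if retention were the same in both, which is not the randomised question.

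Selection adds a second problem. SNS participants reach a permanent implant only after a positive test, and one criterion for a positive test is a 50% improvement in CCIS, itself one of the modelled endpoints. At equal device time, screened SNS responders are compared with unscreened FENIX recipients. The device-time coefficient has no causal meaning either, since people who do badly tend to lose their device.

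At stake is the arm comparison on continence score, constipation score and generic quality of life. Quality of life is one of the trial's stated aims, and these are the main models the article describes for these repeated scores.

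**Working it through.** **The plan's own figure.** The sample size rests only on the primary endpoint and reproduces. For 40% v 60%, two-sided 5% and 90% power, the number per arm is 140 with continuity correction; 2 × 140 = 280, and 280 / 0.8 = 350. Nothing below changes it.

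**Device retention.** From the article: 30% of SNS test patients get no permanent implant, 2–5% of SNS patients are explanted, and 10% of FENIX patients are explanted. Assumed: these percentages apply to everyone randomised, and all FENIX participants are implanted.

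- SNS keeping a device: 100 − 30 − 5 = 65% (68% if explantation is 2%).
- FENIX keeping a device: 100 − 10 = 90%.
- Difference in retention: 0.25 (0.22 if explantation is 2%).

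**Illustration on the CCIS scale.** Assumed: a change of −6 on either device and 0 off it.

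- Total difference, FENIX minus SNS: 0.25 × (−6) = −1.5 points (0.22 × (−6) = −1.32).
- Difference within any device-time category: 0, because both arms have the same outcome there.
- Adjusted treatment effect: 0.

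If people without a device also improve, say by 3 points, the total difference is 0.25 × (−6 + 3) = −0.75, and the adjusted effect is still 0.

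**Unequal benefit on the device.** Put the SNS on-device benefit at 1 (higher is better), the FENIX benefit at b, and give half benefit to those with the device for part of the time. The shares with no, part and full device time are 0.30, 0.05 and 0.65 for SNS, and 0, 0.10 and 0.90 for FENIX.

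- Total effect = b × (0.90 + 0.5 × 0.10) − (0.65 + 0.5 × 0.05) = 0.95b − 0.675. For b = 1 this is 0.275; for b = 1.2 it is 0.465.
- Adjusted effect, when device use is unrelated to prognosis, is a weighted mean of the within-category differences. Each weight is (SNS share × FENIX share) / (sum of the two shares). Full: 0.65 × 0.90 / 1.55 = 0.377. Part: 0.05 × 0.10 / 0.15 = 0.033. None: 0, since only SNS participants are in it.
- For b = 1.2: (0.377 × 0.2 + 0.033 × 0.1) / 0.410 = 0.19.

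The zero weight shows what happens: the 30% of SNS participants who fail the test contribute nothing to the adjusted arm contrast.

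**When device use also tracks prognosis.** A simulation of 400,000 participants per scenario used the same shares, with assumed correlations of 0, 0.3 and 0.6 between device use and prognosis:

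| FENIX on-device benefit (SNS = 1) | Total effect | Adjusted, 0 | Adjusted, 0.3 | Adjusted, 0.6 |
|---|---|---|---|---|
| 1.2 | 0.46–0.47 | 0.19 | 0.05 | −0.08 |
| 1.0 | 0.27 | 0.00 | −0.14 | −0.28 |
| 0.9 | 0.17–0.18 | −0.10 | −0.23 | −0.37 |
| 0.8 | 0.09 | −0.19 | −0.33 | −0.46 |

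The column for correlation 0 agrees with the hand formula. The adjusted value differs from the total effect in every cell. The difference ranges from attenuation to a change of sign.

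**The case against.** The best reply concerns the reading. The sentence has two clauses: the first says what the models adjust for, and the second gives device time a purpose of its own, as something to be studied. It does not literally say that the treatment effect will be taken from a fit containing device time. The article is condensed, and the full protocol or analysis plan may separate the two. This is a possible reading, and it limits how firmly the point can be put. It is not the natural one: the covariate is introduced in the sentence that lists the terms of these models, nothing labels it exploratory, and no model without it is described. The pattern-mixture models do not fill the gap, because setting post-explant data to missing also makes the analysis depend on device status.

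A second reply is that the size is built into the assumptions. That stands. The adjusted value of exactly 0 follows from assuming equal benefit on either device and equal outcome off it. The article says test non-responders are treated according to current practice, so no change off the device is an extreme choice. The benefits and prognosis correlations are not in the article, and the 30% refers to those who undergo the test, not to all randomised to SNS.

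A reader might infer that the covariate is bound to remove or reverse the treatment effect. The article does not support that. With a better on-device FENIX effect (1.2 v 1.0) the result is attenuation at correlations of 0 and 0.3, and the sign changes only at 0.6.

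**Conclusion.** The point holds as a fault in the plan as written. Under the natural reading, the secondary-endpoint models condition on a variable that randomisation itself influences, so their treatment coefficient does not estimate the ITT effect declared in the same section. This conclusion needs only the article's own statements on test failure and explantation.

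The size and sign of the distortion cannot be fixed from the article. Under the assumptions above, the treatment effect is reduced, lost or reversed, depending on how well each device works while in use and how closely device use follows prognosis.

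It would also be wrong to infer that the trial's main result is compromised. The primary logistic model is described with the minimisation factors only, and neither that analysis nor the 350 participants are touched. The point should be corrected but ranks below a must-fix.

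**What to change.** State that the secondary treatment contrasts for SF-12, EQ-5D-5L, CCIS and OD score come from models by randomised arm with visit time and the minimisation factors, without device time. Move device time to a separate analysis, labelled exploratory and non-causal. If the full protocol or analysis plan already separates the two, one sentence saying so is enough.

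The cost is wording only: no further data, participants or visits. It should be settled before any comparison by arm is run, since dropping the covariate after seeing results would look selective.
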